### Statistical analysis

The analysis will be conducted according to the intention-to-treat principle. All participants will be included in the analysis according to group assignment, regardless of adherence. For the analysis of the primary outcome, the number of NSSI episodes during the preceding month, as measured at the 6-month follow-up, we will assess the intervention effect using linear regression with group allocation as the independent variable. If data from more than 5% of the participants are missing at 6 months, we will use multiple imputation to account for missing data. Imputation will be based on baseline NSSI, gender, age, and baseline variables associated with missingness. Secondary analysis will include baseline NSSI, age, gender, and baseline characteristics which differ between groups at baseline. Confidence intervals will be presented as well as significance level. All tests will be two-tailed and *p* values below 0.5 will be considered significant and interpreted with respect to the hierarchy of hypothesis recognizing that all outcomes, apart from the primary, are exploratory.

The analysis will be conducted using SPSS, version 22.0.

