### Enrollment and randomization

Interested individuals will be encouraged to contact the research assistant through phone or e-mail. They will be provided with verbal and written information about the study, in which it is emphasized that participation is voluntary and that they may withdraw their consent at any time. They may take time to consider or discuss the participation with a next of kin before deciding whether to enrol in the study. During the enrollment phase, the potential participants will be interviewed by using the Mini-International Neuropsychiatric Interview (MINI) [32] and informed consent will be collected via an e-mail from REDCap [33] to the secure digital platform e-Boks where Danish citizens receive verified information [34]. The research assistant will make sure to get the informed consent in the enrollment phase. The participant information materials and informed consent form are available from the corresponding author.

After enrollment, participants will be administered the baseline questionnaires. Subsequently, they will be randomly assigned to either the intervention or the control group in a 1:1 allocation, using REDCap’s feature for a computer-generated sequence randomization. The randomization will be stratified by sex and number of NSSI episodes, as measured at baseline by the Deliberate Self Harm Inventory, to avoid overrepresentation of participants with a high number of NSSI episodes in one group. This stratification will be also facilitated through REDCap. The research assistant will generate the allocation sequence in REDCap after enrolling the participant and inform the participant which group, they are assigned to.

As part of the enrollment process, all participants will be informed that they can contact the research assistant in case of questions or technical problems. Participants will also receive information on where they can seek help if needed, for instance through helplines and the emergency services, such as 1318 and 112.

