### Sample size

Based on previous estimates, a reduction of 3.5 NSSI episodes is expected in the intervention group after the 6-month follow-up compared to participants in the waitlist control group at follow-up after 6 months [28, 43, 44]. A post-intervention standard deviation of 9 is assumed based on previous findings [43, 44]. If the true difference between the intervention and control groups is 3.5, a total of 140 participants should be included in each group in order to reject the null hypothesis with a power of 90% and a type I error probability of 0.05, implying a total of 280 participants.

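### The primary model leaves out the stratification factors, so a valid test loses precision; the secondary model adds covariates by chance imbalance

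*Protocol article*

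**What the plan says.** Enrollment and randomization: "The randomization will be stratified by sex and number of NSSI episodes, as measured at baseline by the Deliberate Self Harm Inventory". The reason given is to keep participants with many episodes from being concentrated in one arm, so the authors themselves treat baseline NSSI as prognostic. Allocation is to "either the intervention or the control group in a 1:1 allocation".

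Statistical analysis, primary outcome: "we will assess the intervention effect using linear regression with group allocation as the independent variable". No covariate is named for this model. The same section uses baseline NSSI, gender and age to impute missing outcomes once more than 5% are missing.

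Statistical analysis, adjusted model: "Secondary analysis will include baseline NSSI, age, gender, and baseline characteristics which differ between groups at baseline". The article gives neither a definition of a difference nor a list of candidate variables.

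Outcomes: the same one-month inventory is given at baseline, 3 months and 6 months, so the baseline value of the primary outcome is collected anyway.

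**The concern.** Stratified randomisation makes the arms more alike on the stratifying variables than simple randomisation would. A model with group only still counts the between-stratum variation as noise, so its standard error is too large for the design that was used. The price is an interval wider than necessary and a two-sided test whose true size is below 5%. Separately, omitting a baseline measurement of the outcome itself gives up whatever variance that measurement explains.

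The clause on baseline differences is a second weakness. In a randomised trial, observed baseline differences are chance. Selecting on them says nothing about how strongly a variable predicts the outcome, and the final content of the adjusted model is unknown until the data are seen.

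**Working it through.** **Inputs from the article (Sample size; Statistical analysis).** Difference: "If the true difference between the intervention and control groups is 3.5". Spread: "A post-intervention standard deviation of 9 is assumed based on previous findings". Error rates: "with a power of 90% and a type I error probability of 0.05". Sidedness: "All tests will be two-tailed". There are 140 participants per arm. The Statistical analysis section prints a significance threshold of 0.5; that is a separate matter, and 0.05 is used here.

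**Assumed, not in the article.** Correlation r between baseline and 6-month counts of 0.3 to 0.6; 20% loss analysed as complete cases; for the simulation, normal data, a median split of baseline NSSI, permuted blocks of 4 and 85% women.

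**1. The plan's own figure.** n per arm = 2(1.960 + 1.282)² × 9² / 3.5² = 2 × 10.51 × 6.612 ≈ 139. The t-test version gives 139.92, hence 140, with 90.0% power. A one-sided test would need 114. The stated 140 is therefore a two-sided, unadjusted comparison and takes no credit for baseline adjustment.

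**2. Precision from adjusting for baseline NSSI.** Residual SD = 9√(1 − r²). Half-width = 1.96 × residual SD × √(2/140).

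| r | Variance cut | Residual SD | Half-width (episodes) | n per arm for 90% power |
|---|---|---|---|---|
| 0 | 0% | 9.00 | 2.11 | 139 |
| 0.3 | 9% | 8.59 | 2.01 | 127 |
| 0.5 | 25% | 7.79 | 1.83 | 105 |
| 0.6 | 36% | 7.20 | 1.69 | 89 |

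**3. True size of the group-only test.** If the strata explain a share R² of the outcome variance and are balanced, size = 2(1 − Φ(1.96/√(1 − R²))).

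- Limiting case, in which the strata carry all of the baseline information (R² = r²): 4.0%, 2.4% and 1.4% for r = 0.3, 0.5 and 0.6.
- Median split, simulated with 4,000 trials of 280 participants: 4.6% at r = 0.3 and 3.2% at r = 0.5. With baseline NSSI and sex in the model it was 5.1% and 4.8%. The simulation error near 5% is √(0.05 × 0.95/4000) ≈ 0.3 points.
- Formula check for the median split: it keeps 2/π = 0.637 of the variance of a normal score, so R² = 0.637 × 0.09 = 0.057 gives 4.4%, and 0.637 × 0.25 = 0.159 gives 3.3%. Both agree with the simulation.
- Simulated power with complete data, group-only against adjusted: 90.7% against 91.8% (r = 0.3), and 92.3% against 96.4% (r = 0.5).

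**4. Power if 20% were lost (112 per arm, complete cases).** SE = 9√(2/112) = 1.203, and 3.5/1.203 = 2.910.

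- Adjusted: Φ(2.910/√(1 − r²) − 1.96) = 86.2% (r = 0.3) and 95.3% (r = 0.6).
- Group only, strata giving no balance: Φ(2.910 − 1.96) = 82.9%. The gain is 3.3 to 12.4 points.
- Group only, strata giving full balance: Φ((2.910 − 1.96)/√(1 − r²)) = 84.0% (r = 0.3) and 88.3% (r = 0.6). The gain is 2.2 to 7.1 points.

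The two cases bracket the gain. The size reduction in step 3 and the larger gain of 3 to 12 points rest on opposite assumptions about balance and should not be quoted together.

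**5. The secondary model.** Its covariates fall into two parts. Baseline NSSI, age and gender are named and fixed. The rest is whatever turns out to differ between the arms. Only the second part depends on the data.

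**The case against.** The strongest defence is that this is a matter of efficiency and not an error. The group-only model is fully specified, leaves the analyst no discretion, gives an unbiased estimate and matches the sample size calculation. With complete data the stated 90% power is met without adjustment. All of that stands. A reader might infer that the primary test is biased, invalid or underpowered; the article does not support that, because the direction of the fault is conservative.

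A reader might also infer that the whole adjusted analysis is data-driven. It is not: the covariate most likely to be prognostic, baseline NSSI, is already fixed in it. Selection of the added terms is on baseline variables and not on outcomes, the Blinding section codes the arms A and B until the conclusion is written, and all outcomes apart from the primary are declared exploratory. These safeguards limit the harm. They do not fix the covariate list, and they do not give imbalance any link to prognosis.

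The size of the loss is also open to challenge. The value of r is assumed, and at 0.3 the half-width shrinks only from 2.11 to 2.01. The 20% loss is assumed as well, and the plan would use multiple imputation from baseline NSSI, gender and age, which should recover part of what a complete-case calculation loses. Both points are accepted.

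**Conclusion.** The point holds as a loss of precision in the primary analysis together with one poorly chosen covariate rule in the secondary analysis. At r = 0.3 the loss is small; at r = 0.5 to 0.6 it is material, with a variance cut of 25% to 36%. The true size of the group-only test is plausibly about 4.6% (r = 0.3) to 3.2% (r = 0.5) if baseline NSSI was split at the median. The 1.4% at r = 0.6 is a limit that would need the strata to capture the full baseline score, and categories cannot do that. Under an assumed 20% complete-case loss, adjustment is worth about 2 to 7 points of power with full balance and 3 to 12 with none.

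All of this rests on a roughly linear relation between baseline and 6-month counts, on the assumed values of r, and on stratum cut-points that the article does not give. The change is worthwhile because the data are already collected, but the primary result would be valid without it.

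**What to change.** Make the primary model 6-month NSSI count on group, baseline NSSI and sex. Keep the group-only model as a sensitivity analysis. Delete the clause that adds characteristics differing at baseline. Any further covariates should be named now, on prognostic grounds; variables already recorded at baseline are enough.

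The cost is a documented and dated amendment to the primary analysis, made before unblinding. Trial status reports that enrolment ended in September 2023 and that the last 6-month questionnaire goes out on 22 February 2024, so the amendment should also state that no outcome data by arm had been examined. No new data, visits or participants are needed.

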### Recruitment

We will strive to include individuals with a wide range of NSSI, from those with shorter duration and milder symptoms who might not be in contact with mental healthcare facilities to those with more severe and chronic NSSI who are already attending treatment at Danish mental health facilities. Non-profit organizations, such as Danish Mental Health Fund (Psykiatrifonden), The Danish National Association for Eating Disorders and Self-harm (Foreningen Spiseforstyrrelser og selvskade), and the Danish telephone helpline for people with suicide thoughts (Livslinien), as well as municipal service centres, educational institutions for individuals aged ≥18 years, psychiatric inpatient units and outpatient clinics, and psychiatric and general emergency departments will be contacted with regard to the referral of potential participants. Furthermore, the trial will be announced through non-profit organizations’ websites and social media platforms and presented at educational institutions for individuals ≥ 18 years old. The research assistant responsible for recruitment will routinely visit relevant locations, such as in-patient clinics in the Capital Region of Denmark, and give reminders to participating venues through e-mails and phone calls.

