### Outcomes

The primary outcome, the number of NSSI episodes during the preceding month, will be measured using the validated 17-item Deliberate Self Harm Inventory (DSHI) [35] at the 6-month follow-up (see Fig. 2). This measure includes questions on a number of NSSI episodes for 17 frequently used methods, e.g. cutting, burning, and scratching. As the original inventory uses a recall period of 4 months, a modified version adapted to 1 month will be used. This modification was done to limit any recall bias regarding the number of NSSI episodes [36]. The DSHI questionnaire will be administered at baseline and 3- and 6-month follow-up.

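### The primary model for an over-dispersed episode count is linear regression on group alone: it omits the stratification factors and has no stated safeguard if a few very high counts push the SD above 9

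*Protocol article*

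**What the plan says.** All references are to the protocol article.

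- **Outcomes:** "The primary outcome, the number of NSSI episodes during the preceding month, will be measured using the validated 17-item Deliberate Self Harm Inventory". The inventory covers 17 methods, with recall shortened to one month. The result is a count with a floor at zero and no stated ceiling.
- **Statistical analysis:** "we will assess the intervention effect using linear regression", with allocation as the only term. This is the only confirmatory analysis, since every other outcome is called exploratory. Covariates appear only later: "Secondary analysis will include baseline NSSI, age, gender, and baseline characteristics which differ between groups at baseline". No other model family, transformation, robust or bootstrap error, or rule for extreme counts is named.
- **Enrollment and randomization:** allocation is 1:1, stratified by sex and baseline NSSI count, "to avoid overrepresentation of participants with a high number of NSSI episodes in one group".
- **Recruitment and Criteria for inclusion and exclusion:** "We will strive to include individuals with a wide range of NSSI", from mild to chronic. Entry needs at least two episodes in the past month, with no upper limit.
- **Sample size:** "a reduction of 3.5 NSSI episodes is expected in the intervention group after the 6-month follow-up", with SD 9, 90% power, type I error 0.05 and 140 per arm.

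**The concern.** The design treats participants with very high counts as a threat to comparability and stratifies on baseline count for that reason. The primary model then ignores that information, although it is collected on everyone before randomisation and is used for the imputation and the secondary analysis.

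A linear model on raw counts weights observations by squared distance, so a handful of very frequent self-injurers can set the standard error. Two things are at stake. One is precision given away by leaving out baseline. The other is exposure of the single confirmatory test to an SD above 9, with no pre-specified analysis to fall back on. Because the article states the model, this is a fixed choice and not a detail left to an unseen SAP.

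**Working it through.** **Inputs.** Difference 3.5, SD 9, power 90%, type I error 0.05 and 140 per arm come from Sample size. Two-sided testing comes from Statistical analysis. The control mean, tail shape and baseline correlation are not given, so every simulation below rests on assumed values.

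**1. The stated sample size reproduces.** n per arm = 2(z₀.₉₇₅ + z₀.₉₀)²σ²/δ² = 2(1.960 + 1.282)² × 81 / 12.25 = 139. The t-test version gives 139.9, so 140. Power at 140 = Φ(3.5 / (9√(2/140)) − 1.960) = Φ(3.254 − 1.960) = 0.902.

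**2. Over-dispersion follows from the SD.** The variance is 9² = 81. A Poisson count has that variance only if its mean is 81 episodes a month. Skewness is an inference: with a floor at zero and a mean near or below 9, an SD of 9 needs a long right tail. Simulated negative binomial counts with average within-arm SD 9 had control-arm skewness from 3.3 (control mean 6) down to 1.1 (control mean 15).

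**3. Few participants carry the variance.** In those simulations the top 5% (14 of 280) held 39% to 72% of the residual sum of squares. With Poisson-lognormal counts (control mean 10, median SD about 8 to 22) they held 59% to 88%.

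**4. The planned test is valid.** Its type I error was 0.046 to 0.062 with negative binomial counts and 0.031 to 0.053 with the heavier tails.

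**5. Power at the planned inputs** (difference 3.5, average SD 9, 140 per arm). With negative binomial counts and no covariates (1,500 runs):

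| Control mean | Linear | Negative binomial |
|---|---|---|
| 6 | 95.4% | 95.7% |
| 8 | 93.1% | 93.6% |
| 10 | 92.2% | 92.6% |
| 12 | 91.7% | 91.6% |
| 15 | 91.0% | 91.5% |

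Poisson-lognormal counts were also run with half of the log variance persisting from baseline (400 runs, control mean 6 to 15). Power was 91–96% for unadjusted linear, 94–97% for baseline-adjusted linear, 91–95% for unadjusted negative binomial, and 96–98% for negative binomial with log baseline. The count link without covariates adds almost nothing here, and adjustment adds a little.

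**6. Power of the planned test if the common SD is larger** (formulas of step 1):

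| SD | Power at 140 per arm | n per arm for 90% |
|---|---|---|
| 9 | 0.902 | 139 |
| 12 | 0.684 | 248 |
| 15 | 0.497 | 386 |
| 20 | 0.310 | 687 |

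**7. What a better model recovers under a heavier tail.** Poisson-lognormal counts, control mean 9, control-arm SD 15, difference 3.5, half of the log variance persistent, 400 runs:

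- unadjusted linear: 73%
- baseline-adjusted linear: 77%
- negative binomial with log baseline and robust errors: 86%

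Adjustment within the linear model gives 77 − 73 = 4 points. The adjusted count model gives a further 86 − 77 = 9. In a separate run at SD 15, the count link without baseline gave 73% against 70% for linear.

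The 73% does not conflict with 0.497 in step 6. Here SD 15 applies to the control arm only. With variance m + cm², c = (225 − 9)/81 = 2.667. The app arm (mean 5.5) then has variance 5.5 + 2.667 × 30.25 = 86.2, an SD of 9.3. The average variance is (225 + 86.2)/2 = 155.6, an SD of about 12.5, which lies between the first two rows above 9 in step 6 (12 and 15). The normal formula gives about 65% there. The simulated figure is somewhat higher because the sample SD of a heavy-tailed count usually falls below its population value.

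**8. Standard errors for the count model.** Model-based negative binomial errors gave type I error of 9–18%. Robust errors gave 4.5–6% in one set of runs and 5.5–8.7% in another, so a small-sample correction is needed and part of the power gain in step 7 may reflect this.

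**The case against.** The strongest defence is that the planned analysis does what it was sized to do. With 140 per arm and 1:1 allocation, inference on a difference in means does not need symmetric errors, and the simulations bear this out. At difference 3.5 and SD 9 the planned power is kept. The proposed model family is the one whose default standard errors misbehave. It does not remove the influence of extreme counts either: a negative binomial model with group alone fits each arm's sample mean. The simulations assume a proportional effect, which favours a log link. Stratification already guards against chance imbalance, and baseline enters the secondary analysis. All of this stands, and it limits the size of the point.

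It does not justify leaving baseline and sex out of the primary model, nor having no fallback if the SD exceeds 9.

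Three stronger readings are tempting and not supported:

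- **That linear regression costs power as planned.** It does not at SD 9. The loss depends on a heavier tail, and part of any gain from an adjusted count model comes from the adjustment.
- **That the effect would be uninterpretable.** A difference in mean monthly episodes is a valid randomised contrast and is the quantity in the Sample size section. The fair remark is that one absolute difference describes a mixed population thinly.
- **That imputation would create negative counts.** The article names the predictors for imputation, not the imputation model.

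**Conclusion.** The point holds as one of precision and robustness, not validity. The confirmatory model omits both stratification factors and has no stated protection against a heavy tail. If SD 9 is right, the practical loss is small: power is about 90% or more, and adjustment adds a few points. If the common SD is 12 or 15, power for 3.5 drops to about 68% or 50%. An adjusted count model would recover part of that: 73% to 86% in the scenario with control-arm SD 15.

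Over-dispersion follows from the article's own SD. Skewness is a well-supported inference. The control mean (6 to 15 across the simulations), the tail weight and the persistence of half the log variance are assumptions, so the gain from the count link itself cannot be fixed from the document. The change is worth making because it costs little, but confidence in its size is only moderate.

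**What to change.** Before unblinding, and preferably before any comparison of the two coded groups:

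1. Adjust the primary model for baseline NSSI count (on the log scale in a log-link model) and sex.
2. Preferably make it a negative binomial regression with log link and small-sample-corrected sandwich standard errors. Report the rate ratio together with the model-standardised difference in mean episodes, averaged over participants, so that the result can still be read against 3.5.
3. Keep linear regression with robust or bootstrap standard errors as a pre-specified sensitivity analysis. Alternatively, keep adjusted linear regression as primary and pre-specify the count model as the sensitivity analysis.

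The cost is analysis wording; no new data are needed. The Blinding section keeps the groups coded A and B during analysis, so the change can be made and dated without knowledge of allocation. There are two small downsides. The main effect may become a ratio, and default model-based errors must not be used, so the team should confirm that the named software (SPSS 22.0) offers the corrected ones.

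### The analysis section sets significance at two-tailed p < 0.5, which contradicts the 0.05 type I error used to size the trial; very probably a misprint, but it should be corrected on record

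*Protocol article*

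**What the plan says.** The protocol article mentions an error rate or threshold in two places.

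- **Statistical analysis.** "All tests will be two-tailed", and p "values below 0.5 will be considered significant and interpreted with respect to the hierarchy of hypothesis". The same sentence names the primary outcome as the only outcome that is not exploratory.
- **Sample size.** "If the true difference between the intervention and control groups is 3.5, a total of 140 participants should be included in each group", and this is to give "a power of 90% and a type I error probability of 0.05". The spread is stated as well: "A post-intervention standard deviation of 9 is assumed based on previous findings".

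No other section gives a threshold, and no passage explains or corrects the 0.5. The Statistical analysis section also promises confidence intervals but does not state their level, so they do not settle which figure is meant.

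**The concern.** A threshold for a two-tailed p value is the type I error rate of the test. The analysis section therefore implies a type I error of 0.50, and the sample size section states 0.05. Both cannot hold.

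The sentence at fault is the one that tells the analyst and the reader when the primary result counts as significant. A published protocol is meant to fix that rule before results are seen. As printed, the rule would let a very small difference in self-injury episodes be called significant, and the stated 90% power would not describe the test in the analysis section. According to the Blinding section, the conclusion is written while the groups are still coded A and B, so the threshold is used before unmasking and should be right by then.

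**Working it through.** **Inputs, all from the protocol article.** Difference 3.5 episodes, standard deviation 9, power 90%, type I error 0.05 and 140 per arm (Sample size); two-tailed tests and threshold 0.5 (Statistical analysis); "randomly assigned to either the intervention or the control group in a 1:1 allocation" (Enrollment and randomization).

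**Step 1. Reproduce the stated sample size.** The normal approximation for two means is

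n per arm = 2 × (z_alpha + z_power)² × SD² / difference²

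Here 2 × 81 / 12.25 = 13.224, and z_power = 1.2816 for 90% power.

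| Threshold | z_alpha | Calculation | n per arm | Matches 140? |
|---|---|---|---|---|
| 0.05 two-sided | 1.9600 | 13.224 × 3.2416² = 138.95 | 139 | yes |
| 0.05 one-sided | 1.6449 | 13.224 × 2.9265² = 113.3 | 114 | no |
| 0.5 two-sided | 0.6745 | 13.224 × 1.9561² = 50.6 | 51 | no |
| 0.5 one-sided | 0 | 13.224 × 1.2816² = 21.7 | 22 | no |

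The t-test version at two-sided 0.05 gives 139.92, that is, 140 per arm, exactly as stated. At two-sided 0.5 it gives 49.4, that is, 50 per arm. Of the four options, only two-sided 0.05 returns the planned size.

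**Step 2. Smallest observed difference that counts as significant.** The standard error is 9 × √(2/140) = 1.0757. The critical difference is t(1 − alpha/2, 278 df) × 1.0757:

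- at 0.05: 2.118 episodes;
- at 0.5: 0.727 episodes.

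The second is 0.727 / 3.5 = 21% of the effect that the trial was planned to detect; the first is 2.118 / 3.5 = 61%.

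**Step 3. False-positive rate with no true effect.** By definition it equals the threshold: 50% against 5%, counting both directions. Half of these favour the app: 25% against 2.5%. In 40,000 simulated two-sample t-tests with 140 per arm and standard deviation 9, 49.7% and 5.0% were significant in either direction, and 24.7% and 2.5% in favour of the app.

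**Step 4. Power for 3.5 episodes with 140 per arm.** The t-test gives 90.0% at 0.05, the stated figure, and 99.5% at 0.5.

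**The case against.** The strongest reply is that this is a dropped zero and nothing more. The Sample size section gives an error rate for rejecting the primary null hypothesis, its 140 per arm works only at two-sided 0.05, and the analysis section's two-tailed tests fit that design. A reader can therefore work out the intended value, and a competent analyst would most likely use 0.05. On this view, the 0.73 episodes and the 99.5% power describe a misprint and not a weakness of the design.

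Most of this stands, and it limits what may be claimed. Three stronger readings are tempting, and the document does not support them:

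- *That the sponsor chose a 50% error rate, or that 0.5 is the figure that would be applied.* Nothing says that the analysis section overrides the sample size section, and the arithmetic points to 0.05.
- *That a trial of an ineffective app would be declared positive half the time.* The 50% includes significant results against the app. This is a superiority trial, and the rate in favour of the app under the literal rule is 25%.
- *That the reference to a hierarchy of hypotheses is undefined.* The same sentence supplies two levels, one primary outcome and the rest exploratory. Any finer ordering may sit in an analysis plan that is not shown.

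What does not stand is the inference that nothing needs to be done. The intended value has to be deduced by reworking a sample size calculation, while the sentence written to state the rule states a different one.

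**Conclusion.** The contradiction is real. It is an internal inconsistency, very probably typographical, in the only significance threshold that the analysis section gives. The document's own figures resolve it in favour of two-sided 0.05.

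Read literally, the rule multiplies the type I error by ten (0.5 / 0.05) and cuts the difference needed for significance to about a third (0.727 / 2.118 = 0.34). These consequences follow only if 0.5 were actually used, and the realistic risk of that is small. The correction is nevertheless necessary, because the sentence governs the primary conclusion.

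The critical differences and the power figures assume the planned standard deviation of 9, complete data on 140 per arm and an unadjusted comparison of means. The 50% and 25% do not depend on the standard deviation or the sample size; they need only a test that holds its nominal level and is symmetric between the directions.

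**What to change.** Replace the sentence so that it says, in substance: *tests are two-sided; the primary outcome is significant if p is below 0.05; every other outcome is exploratory.* Publish this as an erratum before the analysis is unmasked. If unmasking has already taken place, the results report should state the correction and justify it by the sample size calculation, which gives 140 per arm only at two-sided 0.05.

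The cost is one sentence. Sample size, design, data collection and analysis model do not change.
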